### Inclusion Procedure

When the patient is admitted to short-stay geriatric care, the investigators in each hospital of the study will first check the inclusion and noninclusion criteria of the patient. Then, they will explain the study to the patient and give the patient an information form. This will all be the responsibility of each center independently.

### Selection and Exclusion of Participants From Study

The inclusion criteria will be patients aged 75 years and older, male or female, living in their own home or a care facility (including independent-living facilities), hospitalized in short-stay geriatric care, and with confirmed receipt of information on the study and their rights, as stipulated by articles L.1122-1 of the French public health code, by 57 of the “Informatique et Libertés” data protection act, and by MR-003 of the French data protection and civil liberties authority (CNIL). The exclusion criteria will be patients aged younger than 75 years or refusing to participate.

### Monitoring

This study will involve no extra examinations or treatment besides traditional practices. The only difference will be the digitization of all medical findings for analysis. Data will be kept confidential and anonymized for analyses. This study will be noninterventional. All interventions will be carried out following normal clinical practices. There will be no unusual risk or specific constraint for participating patients.

### Study Endpoint

The study endpoint will correspond to when the patient is discharged from short-stay geriatric care. The duration of study participation for each patient will be the duration of their short-stay geriatric care.

### Evaluation Criteria

The primary endpoint is the mean duration of hospitalization in short-stay geriatric care. The secondary endpoints are hospital mortality rate, assessment of health status of elderly patients hospitalized in short-stay geriatric wards using different criteria and their outcomes following discharge, describing and comparing how the different hotlines across France function, analyzing the principal responses provided to doctors using the hotline, and improving awareness.

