**Conclusions:**

The results will reveal whether geriatric hotlines provide the most effective management of elderly patients, as indicated by shorter mean hospitalization durations. Shorter hospital durations could lead to a reduced risk of complications—geriatric syndromes—and the domino chain of geriatric conditions that follow. We will also describe different geriatric hotlines from different cities and compare how they function to improve the health care of the elderly and pave the way toward new advances, especially in the organization of the care path.

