Studies have reported that in 20% to 35% of cases, there was no real need for admission to EDs, and outpatient care or planned hospitalizations would have been possible if appropriate geriatric care was available [14]. Therefore, nearly a quarter of these hospitalizations could have been anticipated and prevented. Some studies on hospitalization durations report that patients with initially planned hospitalizations seem to experience longer times being seen and treated in EDs. Furthermore, this significant number of hospitalizations creates financial issues. According to the French High Council for the Future of Health Insurance, an estimated €2 billion are lost due to the segmentation and inadequacy of response, along with unnecessary hospitalizations [15]. Overall, the literature highlights the need to better coordinate outpatient care with hospital services to provide the elderly with access to more effective care [16].

To improve interactions between GP clinics and hospitals, France’s regional health authorities first organized the area as a unit focused on hospital centers incorporating both EDs and short-stay geriatric wards enabling immediate admission. In parallel, the regional health authorities created telephone hotlines designed to enhance GP clinic-hospital interactions with the aim of reducing the number of hospitalizations, particularly by improving the quality of response. The desired outcome was to improve both the care pathways and health status of the elderly. This hotline service was a recent creation (2013) and is still in an experimental form and not yet widespread. Its use still varies widely across the country, and we have yet to gauge its real value.

The primary objective of this study is to describe the health care pathways and status of patients aged 75 years and older hospitalized in short-stay geriatric care and referred via the hotline. The study population will be from different geriatric care hotlines from around France.

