The aims of this study are to describe and compare how the geriatric medicine hotlines function with the goal of standardizing their use and defining ways they can be improved. We will also analyze the principal responses provided to GPs who call the hotlines and improve awareness of this tool. We hypothesize that geriatric hotlines will lead to reduced mean durations of hospitalizations by helping prevent time spent in EDs when it is unnecessary and potentially a risk. Through the use of a direct geriatric hotline diagnostic tool, we believe elderly patients will experience better health care pathways that no longer involve multiple trips to EDs. The hotlines may facilitate better adapted and more appropriate responses to situations that do not necessarily need hospitalization and provide better alternatives (eg, therapeutic medical and social care, outpatient care, consultations, ambulance services, telemedicine).

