### Participants

The study population will be people aged 75 years and older, living in their own home or a care facility (including independent-living facilities), hospitalized in short-stay geriatric care and referred by the hotline in one of the investigating centers. All participants will be fully aware of the study and their rights regarding their participation. All participating patients will give their consent. Participants or a legally authorized representative will receive informational brochures and give their informed oral consent (more visual difficulties and writing for the elderly). All participants will be able, at any moment and by any method, to withdraw from the study.

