### Recorded Variables and Source Data

The study data will be collected directly from the questionnaires as the study progresses. For the first questionnaire (context of calls and solutions proposed), filled out by the hotline geriatric specialist (Textbox 1), health and administrative information will be collected for the study. The health data collected will include the identification of both speakers on the call, patient age, reasons for calling, degree of emergency as perceived by the geriatric specialist and the calling doctor (evaluated by simple scale from 0 to 10; 0 being a null degree of urgency and 10 an absolute urgency), and the responses offered by the geriatric specialist. The administrative data will include call duration (in minutes).

This questionnaire will be anonymous with no identifying criteria. It will be filled out every time contact is made via the hotline, irrespective of what responses are offered by the doctor (referrals to short-stay geriatric care or not).

For the second questionnaire, filled out by the geriatric specialist treating the patient during their hospitalization in short-stay geriatric care following referral from the hotline (Textbox 2), the sociodemographic, health, family, living situation, and location information will be collected for the study.

Sociodemographic data will include the first and last name of the patient, Patient Permanent Identification number, and patient age. These data will be anonymized on entry.

The health data collected will be the reason for hospitalization; number of hospitalizations during the past year; polypharmacy (four or more medications at the same time); biological data [17], including albumin and C-reactive protein levels for assessing nutritional status; and Charlson Comorbidity Index calculation using patient history for assessing the comorbidities of our geriatric population [18-20]; evaluation of activities of daily living (ADL) before hospitalization according to the validated ADL (/6) [21] and instrumental ADL scales (/4) [22]; evaluation of cognitive status using the Mini-Mental State Examination score (/30) [23]; and recommended referral after hospital discharge.

We chose the Charlson Comorbidity Index because it is a validated, reproducible, and simple comorbidity score that measures the impact of age (as there is excess mortality according to age), weighting by age from 1 (50-59 years) to 5 (90-99 years). This score is widely used for geriatrics publications.

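### Mean stay among admitted hotline patients is a valid description, but a shorter mean does not by itself show more effective management

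*Protocol article*

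**What the plan says.** Under Evaluation Criteria: "The primary endpoint is the mean duration of hospitalization in short-stay geriatric care". The Participants section defines the people averaged as those "hospitalized in short-stay geriatric care and referred by the hotline in one of the investigating centers". Study Endpoint limits follow-up to the same stay: "The duration of study participation for each patient will be the duration of their short-stay geriatric care". A call that ends in advice, a consultation or outpatient care therefore adds nothing to the primary endpoint.

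The Introduction gives the hotline a second task. It was created "with the aim of reducing the number of hospitalizations", and it should bring better "responses to situations that do not necessarily need hospitalization".

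The Abstract's Conclusions fix how the endpoint will be read: "The results will reveal whether geriatric hotlines provide the most effective management of elderly patients, as indicated by shorter mean hospitalization durations". The closing paragraph of the Discussion repeats this and extends it to fewer complications and fewer emergency department (ED) visits. The limitations paragraph just before it says that the study is descriptive and has no comparison.

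Data on all calls exist. Of the first questionnaire, Recorded Variables and Source Data says: "It will be filled out every time contact is made via the hotline, irrespective of what responses are offered by the doctor". The Discussion plans to count avoided or deferred hospitalizations. Comparing how the hotlines function is a secondary endpoint, and Statistical Analysis runs every analysis overall and by centre.

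**The concern.** The mean is taken after the hotline has made its admission decision. If one hotline diverts a type of patient that another admits, their mean stays differ even when every admitted patient is managed identically. The same holds for one hotline that changes its practice over time. A change in the mean can therefore reflect who was admitted and not how well they were cared for.

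The article nevertheless attaches an effectiveness conclusion to a shorter mean. The count of avoided hospitalizations and the case-mix variables are collected, but neither is tied to that conclusion. The headline claim is at stake, as is the reading of any centre-by-centre table of mean stay.

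**Working it through.** **The article's own figure.** The Discussion cites a study with mean stays of 11.6 days (direct hotline admission) and 14.1 days (via the ED). The gap is 14.1 − 11.6 = 2.5 days. It compares two routes into the ward. It says nothing about more or less diversion, so it serves here only as a yardstick.

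**Inputs**
- M = 11.6 days, the mean if every referral were admitted. The figure is from the Discussion; using it this way is an assumption.
- p = 20% to 35%, the share of milder cases. The Introduction gives this range for ED admissions that were not really needed; applying it to hotline referrals is an assumption.
- m, the mean stay these cases would have had. The article gives no figure. Assumed 5, 7 or 9 days, with 14 days as the opposite case.
- d, the fraction of the milder cases diverted: one half or all.

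**Formulas**
- Mean among those still admitted = (M − p·d·m) / (1 − p·d)
- Shift = p·d·(M − m) / (1 − p·d)
- Ward days per 100 referrals = 100 × (M − p·d·m), against 1160 with no diversion

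**Two worked lines**
- p = 20%, m = 9, d = 0.5: (11.6 − 0.9) / 0.9 = 11.89 days, a rise of 0.29. Ward days are 1070.
- p = 35%, m = 7, d = 1: (11.6 − 2.45) / 0.65 = 14.08 days, a rise of 2.48. Ward days are 915, a fall of 245/1160 = 21%.

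**Results: mean (shift); ward days per 100 referrals**

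| p | m | Half diverted | All diverted |
|---|---|---|---|
| 20% | 5 | 12.33 (+0.73); 1110 | 13.25 (+1.65); 1060 |
| 20% | 7 | 12.11 (+0.51); 1090 | 12.75 (+1.15); 1020 |
| 20% | 9 | 11.89 (+0.29); 1070 | 12.25 (+0.65); 980 |
| 35% | 5 | 13.00 (+1.40); 1072.5 | 15.15 (+3.55); 985 |
| 35% | 7 | 12.58 (+0.98); 1037.5 | 14.08 (+2.48); 915 |
| 35% | 9 | 12.15 (+0.55); 1002.5 | 13.00 (+1.40); 845 |
| 20% | 14 | 11.33 (−0.27); 1020 | 11.00 (−0.60); 880 |
| 35% | 14 | 11.09 (−0.51); 915 | 10.31 (−1.29); 670 |

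If m = 11.6 the shift is zero. Ward days fall in every row, while the mean rises in six rows and falls in two. The sign of the shift depends only on whether m is below or above M, which the article does not tell us.

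**The case against.** The endpoint fits the stated objective, which is to describe patients hospitalized after hotline referral. The study is called descriptive and a pilot, and its limitations say that there is no comparison. For that purpose the mean among admitted patients is the right quantity. This stands: the Evaluation Criteria section states nothing wrong, and the fault lies in the interpretation given in the Abstract's Conclusions and the closing Discussion.

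The article also handles part of the problem. Every call is recorded, the responses given are a secondary endpoint, avoided admissions will be counted, and the Discussion asks openly whether less fragile patients are the ones admitted. Case-mix measures are collected and multivariate models are planned. This too stands, but none of it qualifies the statement that a shorter mean indicates effectiveness.

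A reader might infer more: that the plan will rank hotlines on mean stay, that one admitting everybody would look best, and that one diverting mild cases must show a longer mean. The documents do not support this. No section says that hotlines will be ranked or judged on mean stay, and nothing says that diverted patients would have had short stays. Nor does an artefact as large as the 2.5-day contrast follow generally. With a 40% mild share and stays of 8 and 14 days, the mean moves from (40 × 8 + 60 × 14)/100 = 11.6 to 14.0 days. That needs a share above the article's 20% to 35% and a contrast between admitting all and diverting every mild case.

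**Conclusion.** The point holds as a fault of interpretation. Mean stay among admitted patients can be reported as a description, but a shorter mean does not show the most effective management, because the hotline's own decisions determine who is averaged.

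The size is conditional on the assumed inputs. Where diverted patients would have had shorter-than-average stays, half diversion raises the mean by about 0.3 to 1.4 days and full diversion by 0.65 to 3.6 days. Only some of the full-diversion cases come near or above the cited 2.5-day gap. If those patients would have stayed 14 days, the mean falls by about 0.3 to 1.3 days over the same diversion range. Either direction defeats the effectiveness reading, so the conclusion does not depend on which assumption is true.

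**What to change.** 1. In the Abstract's Conclusions and the closing Discussion, delete the inference that a shorter mean stay alone shows effectiveness. Report mean stay as descriptive.
2. Wherever centres are compared, show beside mean stay, per centre, the share of calls about patients aged 75 or older for which short-stay geriatric admission was offered. Also show the share sent to the ED, including those sent for lack of beds. The first questionnaire records age and both responses.
3. As a supplementary descriptive figure, give approximate ward days per 100 calls: geriatric admissions offered per 100 calls × mean ward stay. Show both factors, preferably split by reason for calling.
4. Adjust centre comparisons of stay for the case-mix variables already collected: Charlson index, ADL, instrumental ADL and Mini-Mental State Examination. Adjustment reduces differences in who was admitted but does not turn stay into an effectiveness measure.
5. State the limits of the per-call figure. The first form is anonymous and completed per contact, so repeat calls cannot be identified. It records the response offered, which may differ from actual admission. Stay comes only from patients who did not refuse. The mix of advice calls and admission requests differs by centre. The figure is therefore not an effectiveness measure on its own.

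No new data are needed. The cost is a little extra aggregate analysis and a more modest conclusion.

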### Recorded Variables and Source Data

The study data will be collected directly from the questionnaires as the study progresses. For the first questionnaire (context of calls and solutions proposed), filled out by the hotline geriatric specialist (Textbox 1), health and administrative information will be collected for the study. The health data collected will include the identification of both speakers on the call, patient age, reasons for calling, degree of emergency as perceived by the geriatric specialist and the calling doctor (evaluated by simple scale from 0 to 10; 0 being a null degree of urgency and 10 an absolute urgency), and the responses offered by the geriatric specialist. The administrative data will include call duration (in minutes).

This questionnaire will be anonymous with no identifying criteria. It will be filled out every time contact is made via the hotline, irrespective of what responses are offered by the doctor (referrals to short-stay geriatric care or not).

For the second questionnaire, filled out by the geriatric specialist treating the patient during their hospitalization in short-stay geriatric care following referral from the hotline (Textbox 2), the sociodemographic, health, family, living situation, and location information will be collected for the study.

Sociodemographic data will include the first and last name of the patient, Patient Permanent Identification number, and patient age. These data will be anonymized on entry.

The health data collected will be the reason for hospitalization; number of hospitalizations during the past year; polypharmacy (four or more medications at the same time); biological data [17], including albumin and C-reactive protein levels for assessing nutritional status; and Charlson Comorbidity Index calculation using patient history for assessing the comorbidities of our geriatric population [18-20]; evaluation of activities of daily living (ADL) before hospitalization according to the validated ADL (/6) [21] and instrumental ADL scales (/4) [22]; evaluation of cognitive status using the Mini-Mental State Examination score (/30) [23]; and recommended referral after hospital discharge.

We chose the Charlson Comorbidity Index because it is a validated, reproducible, and simple comorbidity score that measures the impact of age (as there is excess mortality according to age), weighting by age from 1 (50-59 years) to 5 (90-99 years). This score is widely used for geriatrics publications.

Family or marital status data will include single or with a partner, and with or without children. The living situation data will be the residence of the patient (own home, independent-living facility, nursing home). Type of living area will be urban, semiurban, or rural.

Context of calls and solutions proposed.

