By analyzing center by center, we will be able to describe each center with the different responses they offer. Ideally, this will help to improve the function of the geriatric hotline for the entire country and pave the way to new advances, especially in the organization of the care path in the long run.

The analysis also will be conducted in two sections. First, the call to the hotline will be analyzed. Did the experience of the doctor responding to the call influence the type of care recommended and the response offered? Does a high level of perceived emergency correlate to hospitalization via the ED? Is the hotline solely used by general medicine doctors? Would it be a good idea to roll out access to the hotline to other hospital specialties? Given the growing issue of population aging, the current geriatric services are not enough to care for all the elderly. This is why specialists are turning more toward other fields for geriatric assessment (eg, oncology, orthopedics). This study will reveal the different responses that can be provided by this tool (the hotline), from therapeutic or medical advice to referrals for hospitalization, ambulance call-outs, consultations, telemedicine, and more.

Second, we will study the profile of patients referred for hospitalization via the hotline to determine the characteristics of those the hotline recommends for admission to improve their health care approach. Does this tool lead to direct hospitalization in short-stay geriatric care for the less-fragile patients who still have some autonomy? Are the motives for admission less serious? We hypothesize that the mean duration of hospitalization will be shorter in cases in which it is planned, which leads to the question of whether the future of hospitalization is influenced by the ways patients are admitted. In their study involving 520 patients, Dijon et al [27] demonstrated that the intrahospital care pathways of geriatric patients referred directly to short-stay geriatric care are shorter and more effective than those experienced by patients who first went through EDs, with significantly shorter mean hospitalizations achieved through direct hotline-referred admissions (11.6 days versus 14.1 days with ED consultation; *P*<.05). Patients admitted to short-stay care via EDs were also the quickest to be rehospitalized in the future.

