Another advantage of our study is its innovative character because there are currently very few studies analyzing geriatric hotlines [25]. In addition, it is observational in nature, which enables many types of procedures from across the country to be analyzed, leading to more standardized approaches.

The study does have limitations, notably its nonrandomized nature. There is no comparison because it is a descriptive study. The quality of the responses will be operator-dependent. Eventually, the goal will be to conduct a second study aiming to compare profiles of elderly patients hospitalized in short-stay geriatric wards via EDs versus those referred via a geriatric hotline. Through the first questionnaire, we will analyze the different responses provided by the hotline (eg, call-outs, consultations, telemedicine, day hospital). We will evaluate the number of hospitalizations avoided or deferred in time following the use of the hotline to reduce inappropriate passage through EDs.

This first study will demonstrate if managing patients by means of a geriatric hotline offers the most effective approach and results in shorter mean hospitalization durations and thus fewer complications and geriatric syndromes and fewer trips to EDs. It will also describe and compare the function of different geriatric hotlines across France to improve health care pathways for the elderly and pave the way toward future advances, such as new modalities of patient management, the development of more appropriate responses to this population, and the reduction of inappropriate visits to emergencies, which we know can be deleterious for the elderly.

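### The call and admission questionnaires share no described key and no admission-route item, so stay and patient profile cannot be related to route of admission patient by patient

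*Protocol article*

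**What the plan says.** All references are to the protocol article.

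**First questionnaire** (Methods, Recorded Variables and Source Data, with Textbox 1). The hotline geriatrician completes it for every contact: "It will be filled out every time contact is made via the hotline, irrespective of what responses are offered by the doctor". On content: "The health data collected will include the identification of both speakers on the call, patient age, reasons for calling", followed by two urgency ratings, the response offered and the call duration. On identity: "This questionnaire will be anonymous with no identifying criteria".

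**Second questionnaire** (same section, with Textbox 2). The ward geriatrician completes it for patients admitted after a hotline referral. Here patients are identified at source: "Sociodemographic data will include the first and last name of the patient, Patient Permanent Identification number, and patient age". The next sentence reads: "These data will be anonymized on entry". Textbox 2 lists length of stay, prior autonomy, cognition, and outcome including death and discharge destination.

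**Questions posed** (Discussion). On stay: "We hypothesize that the mean duration of hospitalization will be shorter in cases in which it is planned". The Discussion also asks whether the way a patient is admitted affects what follows, and whether direct admission goes to the less frail. On calls: "We will evaluate the number of hospitalizations avoided or deferred in time following the use of the hotline".

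**The concern.** The primary objective is to describe care pathways and health status. A pathway runs from the call, through the response, to admission and outcome. As described, the first half is on one form, the second half is on the other, and nothing joins them.

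The study has no group admitted through the emergency department (ED) without the hotline. The only contrast it could make on route and stay is therefore among its own patients: direct bed, deferred admission, or sent through the ED. That contrast needs the route from the call form and the stay from the admission form for the same patient. Without it, the Discussion's questions about planned stays and ways of admission get no patient-level answer, although the planned sample could support one.

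**Working it through.** **Step 1. Where each variable is listed.**

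| Variable | Call form | Admission form |
|---|---|---|
| Response or route offered (bed allocated; deferral in days; ED for lack of beds; ED for urgent care) | yes | no |
| Urgency ratings, responder grade | yes | no |
| Reason for calling | yes | no |
| Patient age | yes | yes |
| Sex | no | yes |
| Name, permanent number | no | yes, anonymized on entry |
| Length of stay | no | yes |
| Death, discharge destination, activities of daily living | no | yes |
| Shared code, or date of call | none listed | none listed |

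Route and stay never appear on the same form. Age is the only shared patient variable. Centre is assumed known for both, because analyses by centre are planned.

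**Step 2. Could centre plus age replace a key?** Take the most favourable case: 250 admissions in a centre, exactly one call for each, and no other calls. If a call is picked at random among those of the same age, an admission in an age group of size k is linked correctly with probability 1/k. Summing 1/k over everyone gives the number of distinct ages, so

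expected share correct = (number of distinct ages) / 250.

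Ages 75 to 105 (105 is an assumed upper limit) give at most 31 values, hence at most 31/250 = 12.4%. A simulation with assumed mean age 86 and SD 5 or 6 gave:

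| Calls per centre (assumed) | Admissions with a unique match | Expected correct links |
|---|---|---|
| 250 | about 1.0% | 9.6 to 10.6% |
| 500 | about 0.4% | 5.1 to 5.5% |
| 1000 | about 0.1% | 2.6 to 2.9% |

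**Step 3. What is lost.** The article gives no SD for stay and no share of planned admissions, so both are assumed: SD 8 to 12 days and planned share 20 to 50%. The difference is borrowed from the study cited in the Discussion: 14.1 − 11.6 = 2.5 days. That study compared direct hotline admission with admission after an ED visit, so the figure is illustrative only. Total N is taken as 1750 (7 × 250) and as the stated 2000.

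Power ≈ Φ(fδ/SE − 1.96), with SE = SD × √(1/n₁ + 1/n₂), δ = 2.5 and f the share of correct links. Wrong links are taken to contribute no difference.

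- Least favourable setting: N = 1750, 20% planned, SD 12. Then n₁ = 350, n₂ = 1400 and SE = 0.717.
  - f = 1: 2.5/0.717 = 3.486, and Φ(1.526) = 0.937.
  - f = 0.1: 0.25/0.717 = 0.349, and Φ(−1.611) = 0.054.
- Most favourable setting: N = 2000, 50% planned, SD 8. Then n₁ = n₂ = 1000 and SE = 0.358.
  - f = 1: 2.5/0.358 = 6.99, and power is above 0.999.
  - f = 0.1: 0.25/0.358 = 0.699, and Φ(−1.261) = 0.104.

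The opposite tail, ignored here, adds about one percentage point at most.

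**Step 4. Avoided hospitalizations.** Reason for calling and response are on the same form. Calls that asked for hospitalization and ended in advice, consultation, outpatient care or deferral can be cross-tabulated with no linkage. That form cannot show whether the patient was admitted later, or whether two calls concerned one patient.

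**The case against.** **The declared analyses do not need linkage.** Mean stay, mortality, health status and discharge outcome come from the admission form; hotline functioning and responses come from the call form. The Statistical Analysis section names comparisons by sex and by type of discharge, both on the admission form. The Discussion announces a two-part analysis, calls first and patients second. This stands, and it limits the point to the Discussion's questions on planned stays and routes.

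**Planned may mean hotline rather than ED.** The sentence is followed by a study of direct versus ED admission, and the Introduction states the hypothesis as avoiding time in the ED. On that reading the obstacle is the absent comparator, which the article concedes and leaves to a second study; a call number would not help. This is a fair reading. It does not cover the question about ways of admission or the one about frailty and direct admission.

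**The article is condensed.** Excluding identifying criteria does not exclude a non-identifying study number. The textboxes look like summary tables, and neither they nor the text are complete: hospitalizations in the past year appear only in the text, walking aids only in the textbox. This stands as a limit on certainty. A reader might infer that no admission at all can be classified by route, or that such analyses are impossible. The article supports only that they cannot be done from the data it describes.

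**Two further inferences fail.** A reader might conclude that avoided hospitalizations cannot be counted; Step 4 shows that they can, though not verified. A reader might also see a contradiction between an anonymous form and the "identification of both speakers on the call". Textbox 1 records the speakers as role categories, which is compatible with anonymity; the wording is merely loose.

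**Conclusion.** The point holds in a limited form. On the data described, route offered, urgency and responder grade cannot be related at patient level to stay, death, autonomy or discharge destination among hotline patients.

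Centre-and-age matching would be right in roughly 3 to 10% of cases under the assumed ages and call volumes, and in at most 12.4% on average in the most favourable case. Under the assumptions of Step 3, power for a 2.5-day difference would be about 94 to 100% with a shared code, against about 5 to 10% with one link in ten correct.

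The conclusion assumes that the full protocol holds no study number, call date or admission-route item that the article leaves out. If it does, a clarifying sentence is enough. The primary endpoint is unaffected. This is a cheap improvement, not a defect that invalidates the study.

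**What to change.** 1. Put a non-identifying call number (centre code plus sequence number) on the first questionnaire and copy it to the second at admission. If one already exists, say so.
2. At minimum, add one admission-route item to the second questionnaire, using the distinctions already in Textbox 1: direct bed; deferred, with days waited; via the ED because no bed was free; via the ED because emergency care was required. For patients already included, complete it retrospectively only where the site can still re-identify them.
3. Report hospitalizations avoided as calls answered without immediate admission, and state that later admissions and repeat calls were not checked. The call number would not fully cure this, because the second questionnaire covers only hotline-referred short-stay admissions.
4. State whether planned means deferred versus immediate admission among hotline patients, or hotline versus ED. If the latter, leave the comparison to the second study.

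The cost is one extra field, a short amendment to the data-protection description, and some record look-up. Because identifiers are removed on entry, recovery for patients already included will be incomplete.
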